### **11.3.2 Exploratory endpoints**

1. Association between expectation of response to acupressure based on the METE questionnaire and observed response based on change in BPI worst pain score will be analyzed using Spearman correlation.
2. The gut microbiota at baseline and after 12 weeks will be analyzed by group. Change in bacterial phyla and genera proportions and Shannon diversity indices over time will be examined using Wilcoxon rank sum tests to compare groups. Principal components analysis will be conducted to display the microbiome space between compare groups. Differences in structure among groups will be assessed using PERMANOVA (permutational multivariate analysis of variance).

We plan to reduce missing data through monitoring of submission of electronic patient-reported outcomes data and reaching out to participants via text, email, or phone as noted above. We will record all reasons for study withdrawal and missing data. We will assess missing data across study groups, covariates and time points and use multiple imputation via chained equations if it is appreciable.

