### **1.3 Exploratory Objectives**

1. To examine the association between expectation of response to acupuncture as assessed with the METE and observed response based on change in BPI worst pain score

*Endpoint: Expectation of response to acupuncture based on the METE questionnaire*

2. To examine the impact of 12 weeks of true acupuncture versus sham acupuncture on stool microbiome in patients with breast cancer taking aromatase inhibitor therapy.

*Endpoint: Change in (a) bacterial phyla, (b) bacterial genera, and (c) Shannon diversity index with 12 weeks of the intervention*

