## 4 ELIGIBILITY CRITERIA

### 4.1 Inclusion Criteria

Yes/No (Response of “no” = patient ineligible)

- 4.1.1 \_\_\_\_\_ Female or male subject aged  $\geq 18$  years
- 4.1.2 \_\_\_\_\_ Taking the currently prescribed aromatase inhibitor therapy (anastrozole, exemestane, or letrozole) for adjuvant or palliative treatment of breast cancer or for chemoprevention for at least 3 weeks and no more than 2 years at the time of enrollment.
- 4.1.3 \_\_\_\_\_ Planning to take the same AI therapy for at least 12 weeks.
- 4.1.4 \_\_\_\_\_ New or worsening joint pain and/or myalgias since starting the AI therapy, with *worst* pain score of at least 4 out of 10 on the BPI over the 7 days prior to enrollment.
- 4.1.5 \_\_\_\_\_ Completion of radiation therapy, if given, for treatment of breast cancer.
- 4.1.6 \_\_\_\_\_ Completion of chemotherapy, if given. Concurrent use of LHRHa therapy, anti-HER2 therapy, bisphosphonate therapy, PARP inhibitor therapy, and CDK4/6 inhibitor therapy is permitted.
- 4.1.7 \_\_\_\_\_ Patients receiving treatment with NSAIDs, acetaminophen, opioids, duloxetine, cannabinoids, gabapentin, and/or pregabalin must have been taking a stable dose for at least 30 days prior to enrollment if they plan to continue the drug during study participation. If they do not plan to take the medication during study participation, they should stop the medication at least 7 days before initiation of study treatment.
- 4.1.8 \_\_\_\_\_ Able to read, understand, and self-complete questionnaires in English.

**4.1.9** \_\_\_\_\_ Able to access WiFi/internet and willing to use an email account or download and use the MyDataHelps app.

**4.1.10** \_\_\_\_\_ Able to provide informed consent and willing to sign an approved consent form that conforms to federal and institutional guidelines.

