#### **6.4 Blinding**

Our IT support person will place the computer tablets—already loaded with either the true or sham acupressure app - and the AcuWands into opaque shipping boxes per our randomization code (i.e., a tablet with the sham acupressure app loaded on it would be placed in a shipping box labeled with a study ID assigned to the sham arm). The outside of the shipping boxes will be labeled with study IDs. This will ensure that only our IT support person and our staff member who is doing the fidelity assessments will be unblinded, but all other study staff and researchers will remain blinded while participants are participating in the 12-week intervention. The IT support person will not be responsible for collecting or analyzing any study data. Participants in the two self-acupressure arms will be blinded as to which acupressure treatment they have been randomized until the 12-week study intervention is complete.

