*Global Ratings of Change (GRC) Scale:* This is a single-item measure to assess the overall change in pain and stiffness since starting study treatment. It is a 7-point Likert scale from -3 to +3. This will be completed at 6 and 12 weeks (and off study if patient discontinues before week 12).

*Mao Expectancy of Treatment Effect (METE):* The METE is a validated 4-item self-report questionnaire rated on a scale of 1-5 (from total disagreement to total agreement), which assesses a patient's expectation that acupressure will relieve her AIMSS symptoms. The instrument had good internal consistency (Cronbach's  $\alpha$  0.95) in a prior study of acupuncture in patients with cancer. Will be completed at baseline.

*Fibromyalgia (FM) Survey:* The FM survey is a combined measure of widespread pain (body map of painful sites) and symptom severity (e.g., fatigue, cognitive problems, headache, poor mood, scores range 0-12), as a self-reported proxy of centralized pain, assessed at baseline. This is a continuous measure with scores ranging from 0-31. Will be completed at baseline.

*Massachusetts General Hospital Acupuncture Sensation Scale (MASS):* consists of twelve predefined descriptors and one subjective component specified by the subjects in their own words to measure levels of *de qi* sensations. *De qi* is a prerequisite term in Traditional Chinese Medicine used to describe sensory stimulation. It has historically been thought to be an indicator of appropriate acupuncture or acupressure treatment and thus relates to therapeutic effectiveness.

In addition to these validated questionnaires, two non-validated surveys will be used to collect information:

*Demographics Questionnaire:* This 5-item survey will be used to collect basic information about sex, race/ethnicity, education, marital status, and income. Participants are given the option of not answering each of the questions.

*Post-intervention Survey:* This non-validated survey will ask participants what type of acupressure they thought they were performing (relaxing acupressure or sham acupressure), whether they felt the benefits they received were worth the time spent performing acupressure, whether they would recommend this intervention to others, and whether they used the AcuWand device.

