#### **11.2 Sample size determination**

With a sample size of 44 evaluable participants (22 evaluable per arm), assuming a standard deviation of difference in worst pain score between treatment groups of 2.3 points, we will have 80% power to detect a reduction of 2 points in worst pain on the BPI at 12 weeks, assuming a 5% significance level. A 2-point improvement in pain is considered a minimal clinically important difference. A total of 50 participants will be enrolled to account for potential dropout, to ensure 44 participants are evaluable for the primary endpoint.

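### The METE-response analysis correlates expectation with raw pain change, without arm or baseline pain; adjusting for both would be a free improvement to an exploratory item

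*Protocol*

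**What the plan says.** Protocol 1.3, objective 1, asks about this relation: "association between expectation of response to acupuncture as assessed with the METE and observed response based on change in BPI worst pain score" (the wording says acupuncture; the intervention is acupressure). Section 11.3.2, item 1, gives the whole method in one sentence: METE and "observed response based on change in BPI worst pain score will be analyzed using Spearman correlation". It names no arm term, no baseline term and no time point. The next item, on the microbiome, does separate the arms: "The gut microbiota at baseline and after 12 weeks will be analyzed by group".

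Four other places bear on the point:
- Section 9.3 on METE: "Will be completed at baseline".
- Section 6.4: "Participants in the two self-acupressure arms will be blinded as to which acupressure treatment they have been randomized".
- Section 4.1.4 sets an entry floor, a worst "pain score of at least 4 out of 10 on the BPI over the 7 days prior to enrollment".
- Section 11.2: "With a sample size of 44 evaluable participants (22 evaluable per arm"), with a 2-point difference, SD 2.3 and 80% power for the primary comparison.

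No power or error rate is stated for the METE correlation.

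**The concern.** Two features of a bivariate correlation with raw change matter here.

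First, if both arms enter one coefficient, the treatment difference that the trial hopes to find becomes extra scatter in the change score and weakens any METE correlation.

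Second, change is week-12 pain minus week-0 pain, so baseline pain sits inside the outcome with a minus sign. The entry floor on worst pain adds regression to the mean. METE is completed at the same visit as the baseline BPI, and three of its four items ask about the same joint pain and stiffness, so some relation between METE and baseline pain is plausible. If there is one, METE correlates with change through baseline severity, whether or not expectation does anything.

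At stake is how this exploratory result can be read. A reader could take a correlation that comes from baseline severity as an effect of expectation, or a real relation could be hidden.

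**Working it through.** **The plan's own figure.** Section 11.2 gives 22 per arm, difference 2, SD 2.3, 5% level. Taking 2.3 as the SD of change, a two-sided two-sample t-test has 80.4% power, so the stated 80% reproduces. There is no such figure for METE. For orientation, the smallest correlation detectable with 80% power is about 0.41-0.42 at n = 44 and about 0.57-0.58 at n = 22.

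**Dilution from pooling.** With equal arms differing by δ, the variance of change grows from SD² to SD² + δ²/4. METE is balanced apart from chance, so the correlation is multiplied by √[SD²/(SD² + δ²/4)].
- δ = 2: √(5.29/6.29) = 0.917.
- δ = 0.92 (the adjusted true-versus-sham difference in the acupuncture trial described in section 2.2): √(5.29/5.5016) = 0.981.

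**Coupling to baseline.** Table 1 in section 2.2 gives SDs at baseline, at week 6 and of change. From these, r(baseline, follow-up) = (s0² + s1² − sc²)/(2·s0·s1), and r(baseline, change) = (r·s1 − s0)/sc.
- Acupressure: (2.56 + 4.84 − 4.00)/(2 × 1.6 × 2.2) = 0.483; (0.483 × 2.2 − 1.6)/2.0 = −0.27.
- Usual care: (3.24 + 4.41 − 4.00)/(2 × 1.8 × 2.1) = 0.483; (0.483 × 2.1 − 1.8)/2.0 = −0.39.

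Table 1 is BPI severity at 6 weeks in women not taking AIs, so it is only a guide to worst pain at 12 weeks here.

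**Rejection at 5% with no expectation effect.** Simulated trials with n = 44, baseline SD 1.7, follow-up SD 2.15, r = 0.48 and an arm difference of 2. The METE-baseline correlation is assumed. Ranges are across separate sets of runs.

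| METE-baseline r | Planned | Given arm and baseline |
|---|---|---|
| 0 | 4.7%-4.9% | about 5% |
| 0.2 | 6.2%-6.6% | about 5% |
| 0.3 | 8.3%-8.5% | about 5% |
| 0.4 | 10.4%-11.0% | about 5% |

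A second setting has SD of change 2.3, baseline-to-week-12 correlations of 0.3 to 0.7 and an arm difference of 2. It has stronger coupling. The planned test then rejects 7%-9% of the time at r = 0.2 and 10%-17% at r = 0.3, against 5%-6% after adjustment. With METE unrelated to baseline pain, the planned test stays at 5%-6%. A chance METE imbalance between arms of 0.25 or 0.5 SD raises it only to about 7% or 9%.

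**Rejection with a real effect** (first setting, 0.7 points less pain per SD of METE):
- METE-baseline r = 0: 46% planned, 57% adjusted. If the arms differ by 0.92, 54% and 57%.
- r = −0.3: 25%-28% planned, 54%-55% adjusted. The link is masked.
- r = +0.3: 65%-66% planned, 50% adjusted. The link is inflated by the same coupling that raises the error rate above.

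In the second setting, with METE unrelated to baseline and an assumed partial correlation of −0.45, power is 55%-67% as planned, 63%-75% given arm only, and 79%-80% given arm and baseline.

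**The case against.** **The text does not say the arms are pooled.** This stands in part. Pooling is inferred from the missing by-group wording, and a SAP could set the coefficient by arm. Splitting by arm removes the dilution but leaves the coupling to baseline, since the outcome is still raw change.

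**The objective asks for an association with change, and Spearman estimates that.** This is the best point on the other side, and it stands. The unadjusted coefficient is a valid description of the stated association. It is a poor answer only to whether expectation matters beyond baseline severity and arm. That is why it can be kept beside the adjusted estimate.

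**The size rests on an unknown correlation.** This stands. The documents give no METE-baseline figure, and Table 1 is another item, time point and population.

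A reader might infer three stronger claims that the documents do not support:
- That mixing the arms by itself produces a false link. It does not: METE is measured once, at baseline, in blinded participants, and error stays near 5% when METE is unrelated to baseline pain.
- That the planned test always has less power. At a positive METE-baseline correlation it rejects more often, although part of that excess is bias.
- That this analysis is used to interpret the main result. No section says so. The primary result comes from the GEE model, and blinding is checked by a separate chi-square test (11.3.1).

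**Conclusion.** The point holds as a low-severity improvement to one exploratory analysis. As written, the method ignores arm and baseline pain. The dilution from pooling is about 8% of the correlation if the full 2-point effect is real, and about 2% at 0.92 points. The coupling to baseline matters more, but only if METE is related to baseline pain. Over an assumed |r| of 0.2 to 0.4, with coupling like that in Table 1, rejection with no expectation effect is about 6%-12%, and higher if the coupling is stronger. A real link may be masked or inflated according to the sign. If METE is unrelated to baseline pain, there is no false link, and the adjusted analysis gains power: about 11 points in the first setting at a 2-point arm difference, and about 3 points at 0.92.

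**What to change.** Replace item 1 of 11.3.2 with, for example: *The association between METE total score and response will be estimated by the partial Spearman correlation of METE with week-12 worst joint pain, given study arm and week-0 worst joint pain. The estimate and its 95% confidence interval will also be shown within each arm, as description.* A linear regression of week-12 worst pain on METE, arm and week-0 worst pain would serve equally well.

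The unadjusted Spearman correlation with change may stay as a descriptive figure, since the objective in 1.3 is worded in terms of change. Within-arm estimates rest on about 22 participants each and will be imprecise.

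The cost is a short rewording and two degrees of freedom. Arm, METE, and week-0 and week-12 worst pain are already collected. The new text also names the time point, which item 1 leaves out.

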## **12 DATA SUBMISSION SCHEDULE**

The Case Report Forms (CRFs) are a set of (electronic or paper) forms for each patient that provides a record of the data generated according to the protocol. These forms will be completed on an on-going basis during the study. The medical records and self-report from the patient, when appropriate, will be source of verification of the data. The CRFs will be completed by the Investigator or a member of the study team as listed on the Delegation of Duties Log.

## **13 SPECIAL INSTRUCTIONS**

### **13.1 Patient-reported questionnaires**

Prior to the first time the patient completes the questionnaires: Patients should be directed to report all symptoms and limitations whether or not they are related to the cancer or its treatment. Discourage family members from influencing patient responses to the questions. They should also be told that their treating provider will not be told about symptoms that they report on the questionnaires, and if they are bothersome they should mention them to their treatment team.

Whenever possible, questionnaires will be completed online, although if a participant states that they are unable or unwilling to complete the questionnaire online then the questionnaires can be completed by phone.

Participants will be sent notifications, texts, or emails, as appropriate, that questionnaires are available to questionnaires 2 days before each scheduled assessment time at baseline and weeks 6 and 12. If they have not completed the questionnaire by the scheduled assessment time they will be sent a reminder by text, email and/or phone. If they do not answer the questions by 2 days after the assessment they will be contacted by the study coordinator to complete them by phone.

## **14 ETHICAL AND REGULATORY CONSIDERATIONS**

### **14.1 Informed consent**

Informed consent will be obtained from all research participants prior to performing any study procedures using the most recent IRB-approved version.

## **14.2 Human Subjects Protections**

### **14.2.1 Rationale for Subject Selection**

This clinical trial is open to all patients with AIMSS with minimal restrictions in order to permit inclusion of as broad a population as possible. Only patients who read English will be enrolled because the study app is not available in other languages.

### **14.2.2 Participation of Children**

Patients must be at least 18 years of age to participate.

## **14.3 Institutional Review**

Before implementing this study, the protocol, the proposed informed consent form and other information to be provided to subjects, must be reviewed and approved by a properly constituted IRB. Any amendments to the protocol must be reviewed and approved by the IRB.

## **14.4 Data and Safety Monitoring Plan**

This study will be monitored in accordance with the NCI approved University of Michigan Rogel Cancer Center Data and Safety Monitoring Plan.

The study team will meet every six months or more frequently depending on the activity of the protocol. The discussion will include matters related to the safety of study participants (SAE/UaP reporting), validity and integrity of the data, enrollment rate relative to expectations, characteristics of participants, retention of participants, adherence to the protocol (potential or real protocol deviations) and data completeness. At these regular meetings, the protocol specific Data and Safety Monitoring Report form will be completed and signed by the Principal Investigator or by one of the co-investigators.

Data and Safety Monitoring Reports will be submitted to the University of Michigan Rogel Cancer Center Data and Safety Monitoring Committee (DSMC) every six months for independent review.

## **14.5 Adverse Events**

### **14.5.1 Experimental Therapy**

Few adverse events are expected from this non-pharmacologic, non-invasive study intervention.

### **14.5.2 Adverse Event Reporting Requirements**

Adverse event (AE) monitoring and reporting is a routine part of every clinical trial and is done to ensure the safety of subjects enrolled in the studies as well as those who will enroll in future studies using similar agents. Data on adverse events will be collected from the time of the initial study treatment through the last administration of study treatment. Any serious adverse event that occurs after

the last study treatment and is considered related to the study treatment must also be reported. Serious Adverse Events (SAEs) will continue to be followed until:

- Resolution or the symptoms or signs that constitute the serious adverse event return to baseline;
- There is satisfactory explanation other than the study treatment for the changes observed; or
- Death.

The investigator is responsible for the detection, documentation, grading and assignment of attribution of events meeting the criteria and definition of an AE or SAE. The definitions of AEs and SAEs are given below. It is the responsibility of the principal investigator to ensure that all staff involved in the trial is familiar with the content of this section.

Any medical condition or laboratory abnormality with an onset date before initial study intervention initiation is considered to be pre-existing in nature. Any known pre-existing conditions that are ongoing at time of study entry should be considered medical history.

All events meeting the criteria and definition of an AE or SAE, as defined in Section 15.5.3, occurring from the initial study intervention initiation to the last administration of the study intervention must be recorded as an adverse event in the patient's source documents and on the CRF regardless of frequency, severity (grade) or assessed relationship to the study treatment, except as outlined below.

In addition to new events, any increase in the frequency or severity (i.e., toxicity grade) of a pre-existing condition that occurs after the patient begins study treatment is also considered an adverse event.

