## **6.7 Duration of Therapy**

Patients will be treated with self-acupressure for 12 weeks (+/- 2 days).

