### **6.7.1 Criteria for discontinuation of treatment (“off treatment”)**

The following will result in study treatment discontinuation:

- Discontinuation of AI therapy, defined as:
  - Discontinuation of the currently prescribed AI therapy for more than 7 days
- Evidence of new cancer, cancer recurrence, or cancer progression
- Unacceptable toxicity (see section 8.1)
- Delay of 14 consecutive days of study treatment (acupressure) due to any reason
- Initiation of acupuncture
- The participant may discontinue study treatment (acupressure) at any time for any reason including participant request to be withdrawn from study
- Death

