| Debriefing                                   |                                   |                              |                                               |                                            |                                                | X l                                       |

a. All screening procedures can take place remotely, via phone, text, or email. The informed consent can be completed remotely using SignNow or other IRB-approved platform, or can be completed in person.

b. Baseline visit can take place up to 4 weeks after the screening visit and will take place remotely. The study coordinator will contact the participant and conduct the baseline visit via phone or Zoom once the participant has received the device and AcuWand. The patient should start the study intervention within 2 days of the baseline visit.

c. Timed based on baseline visit.

d. As per section 6.7.1, if participants discontinue AI and/or study intervention they should continue to complete patient-reported questionnaires as originally planned, timed based on baseline visit. If they have been off AI and/or study intervention by more than 4 weeks at the time of 12 week study assessment, stool collection should not take place.

e. Participants will be to self-report their cancer medical history (date of diagnosis, disease stage, surgery type and date, chemotherapy type and dates if given, radiation dates if given, and names and approximate dates of all prior endocrine therapy). Participants will also be asked to submit copies of medical records if possible to verify the information.

f. Study phone calls will be performed at baseline and weeks 6 and 12. At baseline visit, study coordinator will confirm that the participant has received the tablet and AcuWand, and answer any questions that have arisen. At weeks 6 and 12, study coordinator will assess adverse events. At all visits, study coordinator will assess concomitant medications (including pain medications, antidepressants, anxiolytics, sleep medication, and use of AI therapy) based on participant self-report.

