### **9.2.2 Evaluation during study participation**

- Daily, participants will complete an electronic study diary to report use of the study intervention and AI therapy.
- Weekly, participants will be asked to complete two questions either electronically or by phone about worst and average pain severity.
- At 6 and 12 weeks (+/- 2 days), participants will undergo assessment with a battery of electronic questionnaires. If a patient is unable to complete them electronically, they will be asked by phone.
- At 6 and 12 weeks (+/- 2 days), participants will have a virtual study visit with a study coordinator (phone or video) to review concomitant medications and adverse events. If a patient is unable to complete a visit by phone or video, they will be asked by email.
- During week 12 (or at off study if a participant discontinues study participation early), participants who submitted optional baseline stool samples will be asked to undergo repeat optional stool sample collection. If a participant does not collect a sample, or does not submit it for analysis, it will not be considered a deviation.

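### Section 14.5.2 closes adverse-event recording at the last acupressure session, which conflicts with the week-6 and week-12 adverse-event reviews and leaves early stoppers' later events largely unrecorded

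*Protocol*

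**What the plan says.** Section 14.5.2 sets the window twice. On collection: "Data on adverse events will be collected from the time of the initial study treatment through the last administration of study treatment". On entry in source documents and the case report form, events meeting the definition and "occurring from the initial study intervention initiation to the last administration of the study intervention must be recorded as an adverse event". No days are added after the last session. The only extension is for a serious event that occurs after "the last study treatment and is considered related to the study treatment must also be reported".

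Other parts of the protocol run to week 12 whether or not treatment continues:

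- Section 8, footnote d: "if participants discontinue AI and/or study intervention they should continue to complete patient-reported questionnaires as originally planned".
- Section 8, footnote f: "At weeks 6 and 12, study coordinator will assess adverse events".
- Section 9.2.2, at weeks 6 and 12 (within 2 days): "participants will have a virtual study visit with a study coordinator (phone or video) to review concomitant medications and adverse events".
- The secondary-endpoint text (headed 12.3.2, within section 11.3), item 5, has safety assessed for the duration of the trial and adverse events reported descriptively.

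Section 6.7.1 lists several routes to stopping acupressure before week 12, among them unacceptable toxicity, participant choice and "Delay of 14 consecutive days of study treatment (acupressure) due to any reason".

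**The concern.** The recording rule follows exposure, while the contact schedule follows the calendar. For someone who stops early, the two separate. The coordinator is told to ask about adverse events at weeks 6 and 12, but section 14.5.2 does not require what is heard to be recorded if the event began after the last session and is neither serious nor, if serious, related. Coordinators could resolve this differently from one participant to the next.

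Footnote d adds a second uncertainty. It names only questionnaires as continuing after discontinuation, so a reader cannot be sure that the adverse-event calls continue as well.

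At stake is whether the adverse-event table covers 12 weeks for everyone who started or a length of time that varies with how long each person kept going. If stopping differed between true and sham acupressure, descriptive counts per arm would rest on different amounts of observation. An analysis plan could adjust for time observed, but it could not recover events that were never recorded.

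**Working it through.** **1. The passages side by side.** Take a participant who stops at the end of week 2, stays in follow-up, and has a new non-serious event in week 8.

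| Source | What it implies for this event |
|---|---|
| Section 8, footnote d | Participant still completes questionnaires to week 12 |
| Section 8, footnote f; section 9.2.2 | Coordinator asks about adverse events at week 12; no off-treatment exemption |
| Secondary endpoints, item 5 | Safety covers the trial, so the event would be expected in the report |
| Section 14.5.2 | Onset is after the last session and the event is not serious, so recording is not required |

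The first three rows and the last cannot all be followed to a consistent result. An unrelated serious event gives the same outcome. A related serious event does not, because section 14.5.2 keeps it reportable.

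**2. How much time is affected.** The protocol states no figure for adverse-event observation time, so there is nothing to reproduce. The inputs are:

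- N = 25 per arm (Study Summary)
- W = 12 weeks of treatment (section 6.7)
- d = share of an arm that stops acupressure early: **assumed**
- s = mean week of stopping: **assumed**, 2 to 8

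Full observation is N × W = 25 × 12 = 300 participant-weeks per arm.

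Time outside the window per arm = N × d × (W − s).

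With d = 10%, borrowed from the dropout figure in section 3.2:

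| s | Participant-weeks outside the window | Share of 300 |
|---|---|---|
| 8 | 25 × 0.10 × 4 = 10 | 3.3% |
| 6 | 25 × 0.10 × 6 = 15 | 5.0% |
| 4 | 25 × 0.10 × 8 = 20 | 6.7% |
| 2 | 25 × 0.10 × 10 = 25 | 8.3% |

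**3. Whether the arms differ.** Observed time per arm = N × (W − d × (W − s)).

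- Equal stopping, 10% in each arm, s = 2: 275 against 275, ratio 1.00. The ratio is 1.00 at every s.
- Unequal stopping, assumed 5% against 20%, s = 8: 25 × (12 − 0.05 × 4) = 295 against 25 × (12 − 0.20 × 4) = 280, ratio 0.95.
- The same shares, s = 2: 25 × (12 − 0.05 × 10) = 287.5 against 25 × (12 − 0.20 × 10) = 250, ratio 0.87.

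**4. With one window to week 12.** Each arm contributes 300 participant-weeks whatever the stopping pattern, provided those who stop acupressure remain in contact.

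**The case against.** The best defence is that on-treatment collection is a legitimate choice. Section 14.5.3 defines an adverse event in terms of a patient receiving study treatment, which matches the window. Sections 10.1 and 14.5.1 expect few events from a non-invasive intervention, and related serious events stay reportable. Safety is not among the listed objectives, and no between-arm test of adverse events is planned. All of this stands, and it keeps the point small. It does not remove the conflict with footnote f, section 9.2.2 and the secondary-endpoint text.

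The documents do not support several stronger readings that a reader might infer:

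- *All later events of early stoppers are lost.* Related serious events are kept, and the scheduled reviews carry no off-treatment exemption. The text contradicts itself rather than imposing a uniform cut-off.
- *The problems that make people stop go unrecorded.* Such a problem normally begins at or before the last session, inside the window. A later flare of aromatase-inhibitor joint pain is also a poor example: section 14.5.3 excludes it from adverse-event reporting unless serious and leaves it to the questionnaires.
- *One arm loses about 13% of its observation.* That figure needs all 5 expected dropouts (10% of 50) to fall in one arm and stop at week 4: 5 × 8 = 40 of 300 participant-weeks. With equal stopping, the chance that all 5 fall in the same arm is 2 × C(25,5) / C(50,5) = 106,260 / 2,118,760, about 5%. It also treats dropout as stopping acupressure. A person who leaves the study altogether gives no later adverse-event data under any window.
- *Completers are materially affected.* With the week-12 call 2 days early and the last session 2 days late, 4 of 84 days go unasked. That is a corner case.

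**Conclusion.** The point holds as an inconsistency in the data-collection rules with a modest consequence. Section 14.5.2 ends recording at the last session, while the calendar, the procedures section and the safety endpoint run to week 12. Followed literally, later non-serious and unrelated serious events in people who stop early need not be recorded.

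The illustrative size is 3.3% to 8.3% of participant-weeks per arm, if 10% stop early at a mean of week 8 down to week 2. Both inputs are assumptions, and the 10% is a dropout figure used as a stand-in. A reader might go further and infer that the safety comparison is biased. The documents do not show that: equal stopping gives no imbalance, no stopping rates by arm are given, and adverse events are only described. The 0.87 to 0.95 ratio applies only to an assumed 5% against 20%. The primary endpoint is untouched. It is worth correcting because the change is cheap and events that go unrecorded cannot be recovered at analysis.

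**What to change.** Reconcile section 14.5.2 with section 8, section 9.2.2 and the safety item in the secondary-endpoint text:

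1. In both window statements of section 14.5.2, record adverse events from the first session through the week-12 call for every participant who starts, whether or not acupressure has stopped. Keep the existing provision for later related serious events.
2. In section 8, footnotes d and f, state that the week-6 and week-12 calls, including the adverse-event review, continue on the original schedule after discontinuation.

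This is a wording change that uses contacts already scheduled. Its cost is that some events unrelated to acupressure will be recorded after it has stopped. The attribution categories in section 14.5.4 already deal with those.
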